## Abstract

**Background:**

The emergency department has been identified as an area within the health care sector with the highest reports of violence. The best way to control violence is to prevent it before it becomes an issue. Ideally, to prevent violent episodes we should eliminate all triggers of frustration and violence. Our study aims to assess the impact of a quality improvement multi-faceted program aiming at preventing incivility and violence against healthcare professionals working at the ophthalmological emergency department of a teaching hospital.

**Methods/Design:**

This study is a single-center prospective, controlled time-series study with an alternate-month design. The prevention program is based on the successive implementation of five complementary interventions: a) an organizational approach with a standardized triage algorithm and patient waiting number screen, b) an environmental approach with clear signage of the premises, c) an educational approach with informational videos for patients and accompanying persons in waiting rooms, d) a human approach with a mediator in waiting rooms and e) a security approach with surveillance cameras linked to the hospital security. The primary outcome is the rate of incivility or violence by patients, or those accompanying them against healthcare staff. All patients admitted to the ophthalmological emergency department, and those accompanying them, will be enrolled. In all, 45,260 patients will be included in over a 24-month period. The unit analysis will be the patient admitted to the emergency department. Data analysis will be blinded to allocation, but due to the nature of the intervention, physicians and patients will not be blinded.

**Discussion:**

The strengths of this study include the active solicitation of event reporting, that this is a prospective study and that the study enables assessment of each of the interventions that make up the program. The challenge lies in identifying effective interventions, adapting them to the context of care in an emergency department, and thoroughly assessing their efficacy with a high level of proof.

The study has been registered as a cRCT at clinicaltrials.gov (identifier: NCT02015884).

## Background

### An increase in violence at hospitals and more specifically at emergency units

The National Institute for Occupational Safety and Health has long recognized violence as a workplace hazard for health care workers [1]. The emergency department (ED) and treatment rooms are among the most frequent locations for violent events to take place in the health care setting. Around the world, the ED has been identified as an area within the health care sector with the highest reports of violence [2,3]. In the United Kingdom, it was found that 50% of attacks against health care workers occurred in the ED [4]. High rates of workplace violence have also been experienced by ED nurses in the United States of America [2], in Australia [5] and in Ireland [6]. The current rate of violence towards staff in the ED is reported to be 2.0 to 2.8 incidents per 1,000 patients, and is rising [7,8]. However, most of the violent episodes in the ED go unreported [8].

In France, the National Observatory of Violence in Healthcare Facilities (Observatoire National des Violences en milieu de santé) received 11,344 reports of violence (against people or property) in 2012 from 352 hospitals. This is nearly double the number of reports compared to 2011 (in part due to the higher number of reporting facilities). Among all reported violence, the vast majority, 85%, involve personal aggressions [9]. Teaching hospitals were amongst the facilities most affected, as were EDs (14% of reports). Those responsible for reported violence were generally patients (73%), or those accompanying them (28% of the violence in the EDs), whereas hospital staff were the victims in 77% of cases. Those working at healthcare facilities are particularly exposed to the risk of workplace violence [10,11].

### Types and consequences of workplace violence

When attempting to describe violent behavior, three levels of aggressiveness are distinguished by order of severity: incivility, which results from a lack of respect for others and manifests itself as relatively harmless acts, verbal abuse or physical threat (insults, threatening behavior) and physically violent acts [12]. This incivility/violence can have repercussions on the physical and/or emotional health of the victims, and thus on their well-being and the quality of their work. Staff have been shown to suffer emotional symptoms similar to post-traumatic stress disorder, job dissatisfaction, and early feelings of burnout, while hospitals suffer the financial burden of decreased productivity and excessive lawsuits [4,5,13-19].

### Precipitators of violence and aggression

Different factors, such as anxiety, boredom, lack of information, lack of understanding of triage times and categories, and waiting times, may influence violent behavior [2,5,20,21]. While patients themselves are frequently the main aggressor, relatives and visitors are also known to instigate violence.

The best way to control violence is to prevent it before it becomes an issue. Ideally, to prevent violent episodes we should eliminate all triggers of frustration and violence.

### Objective

The study aims to assess the impact of a violence prevention program geared to reducing the incivilities or violence against health care workers in an ophthalmological emergency department (OED) at a teaching hospital. Our prevention program was designed in order to minimize the discomfort of patients visiting the OED.

## Methods

### Study design

This quasi-experimental study is a single-center prospective, controlled time-series study with an alternate-month design (On and Off periods). The prevention program combines 5 complementary interventions that are implemented step by step (interventions A to E, phase 1 - see Figure 1). Each intervention has no residual effect during Off periods and is independent of the others. Each intervention is based on a design that alternate two one-month On (intervention) and Off (control) periods over a total of four months. After the 4-month On/Off period, each intervention becomes permanent alongside the previously implemented interventions.

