### Sample size calculation

The number of patients has been calculated based on following hypotheses:

A 20% initial rate of incivility/violence against OED staff, whatever the severity of the violence,

A minimum 2.5% reduction in incivility/violence with each new intervention A to E,

An average of 62 patients per day expected,

The independence of the 5 interventions,

A risk alpha of 5% and the statistical power of 80%.

The statistical unit is the patient admitted to the OED. Using the Casagrande and Pike method [23], and based on the aforementioned hypotheses, the sample size required is 30,224 patients for the 5 alternating intervention phases (see Table 2).

**Table 2 T2:** Sample size required by intervention phase

**Interventions**	**TControl**	**TIntervention**	**Sample size required**
Intervention A	20%	17,5%	7802
Intervention B	17,5%	15%	6986
Intervention C	15%	12,5%	6108
Intervention D	12,5%	10%	5166
Intervention E	10%	7,5%	4162

Note:

TControl is the rate of incivility/violence in the control group (Off).

TIntervention is the rate of incivility/violence in the intervention group (On).

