## Discussion

### Discussion of study design

The strengths of this study include active solicitation of event reporting, the fact that this is a prospective study and the study design enabling assessment of each intervention in the program.

In certain situations, it may be of interest to use an alternate-month study design, i.e. alternating On (intervention) and Off (control) periods which provide a series of before and after studies with interventions repeated over time [25]. This type of study design can be used only when there is no residual affect during Off periods. It is particularly well-suited to assess the impact of IT tools [26]. This design may be of particular interest when assessing the impact of an intervention in a single health care facility, which makes a randomized controlled study difficult to perform [27].

Unlike a simple before/after study, this design offers the advantage of providing a control group that enables more thorough assessment of the impact of a repeated intervention at a health care facility.

Moreover, in addition to the overall effect, the effect of each of the 5 interventions can be assessed. It nonetheless requires the event measured to be sufficiently frequent during each alternating period.

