### Discussion of primary outcome criterion

All of the healthcare staff at the OED were trained to report acts of incivility/violence for each patient and/or relative coming to the unit. A number of scales exist to measure violence, such as the Overt aggression scale [28]. We created a scale based on the findings of the French National Observatory of Hospital violence [9]. Unlike other studies, which consider only physical violence, our scale also takes into account verbal abuse and rudeness. Although verbal abuse is often not included [29], most studies consistently show that verbal abuse, threats and assaults are common [13,30,31].

However, perceptions of what constitutes ‘abuse’, ‘threats’ or ‘assault’ may be less clear, which may have an impact on the reporting and subsequent handling of such incidents [32]. The under-reporting of incivility/violence is a well-known phenomenon, namely when reports are made directly to the hospital administration [18,32-35]. Lack of time is the main reason for under-reporting given by healthcare professionals. The fact that incivility often goes unrecognized, due to habit and understanding of/empathy for patients, is also mentioned. In order to curb this under-reporting, healthcare professionals were trained using virtual cases (short clinical vignettes) in order to provide all staff enrolled in the study with a shared definition of incivility or violence (see Table 1). In addition, any act of incivility/violence toward healthcare care staff or other patients was recorded in the patient’s medical record, simultaneously alongside other essential medical information.

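### Strict monthly alternation leaves a one-month On/Off time offset in every block, the planned per-block Khi-2 test does not adjust for it, and the cRCT label conflicts with the quasi-experimental design described

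*Protocol article*

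**What the plan says.** Study design describes the study as follows: "This quasi-experimental study is a single-center prospective, controlled time-series study with an alternate-month design (On and Off periods"). Within each intervention's block, "Each intervention is based on a design that alternate two one-month On (intervention) and Off (control) periods over a total of four months". After its block, the intervention becomes permanent. No passage describes a random choice of months, order or starting state.

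Data analysis specifies a Khi-2 test of On against Off in each of the five intervention phases. Mixed models with confounders are named only for phase 2 against phase 0.

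The outcome is reported by staff (Primary outcome), who know which phase they are in (Blinding). Discussion of primary outcome criterion acknowledges that "The under-reporting of incivility/violence is a well-known phenomenon".

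On the label, the Discussion paragraph of the Abstract says: "The study has been registered as a cRCT at clinicaltrials.gov". Discussion of study design presents alternation as useful in a single facility, "which makes a randomized controlled study difficult to perform".

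**The concern.** Alternation spreads both states over the block but does not centre them on the same date. If the reported rate moves steadily over calendar time, for whatever reason, part of that movement appears as an On-Off difference, and a plain Khi-2 cannot separate the two. A staff-reported, unblinded outcome collected for 24 months after a preparatory awareness campaign is one where such movement is plausible. Depending on which state comes first and which way reporting drifts, the result could be a false benefit, a false harm or a masked benefit.

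The label matters for a different reason. A reader or meta-analyst who sees cRCT will credit the study with random allocation, which the Methods do not describe.

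**Working it through.** **Inputs.**
- Phase 1 enrols 37,820 patients over 20 months (Time frame): 37,820/20 = 1,891 per month, or 3,782 per state per block.
- Starting rate: "A 20% initial rate of incivility/violence against OED staff". The target is 2.5 points per intervention, with alpha 5% and power 80% (Sample size calculation).
- The drift b is not given in the documents. It is assumed linear, at 0.3 or 0.5 points per month, with 1.0 as an outer value.

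**The plan's own figure.** The two-sided, continuity-corrected two-proportion formula gives 7,810, 6,994, 6,114, 5,172 and 4,168, total 30,258. Table 2 totals 30,224, a difference of 0.1%. One-sided versions do not reproduce it, so the test is taken as two-sided at 5%.

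**Time offset.** Number the months of a block 1 to 4.

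| Order | Mean On | Mean Off | Offset (months) |
|---|---|---|---|
| Off-On-Off-On | (2+4)/2 = 3 | (1+3)/2 = 2 | +1 |
| On-Off-On-Off | 2 | 3 | -1 |
| Off-On-On-Off | 2.5 | 2.5 | 0 |
| On-Off-Off-On | 2.5 | 2.5 | 0 |

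Strict alternation allows only the first two rows. The bias is b × 1 month: 0.3/2.5 = 12% and 0.5/2.5 = 20% of the target.

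**Effect on the test, no true effect.** SE = √(2p(1-p)/3,782). Rejection probability = Φ(-1.96 - b/SE) + 1 - Φ(1.96 - b/SE).
- p = 20%: SE = √(2 × 0.16/3,782) = 0.92 points. For b = 0.3, b/SE = 0.33 and rejection is 6.2%. For b = 0.5, b/SE = 0.54 and rejection is 8.4%. For b = 1.0, rejection is 19%.
- p = 10%, a rate Table 2 expects in later blocks: SE = √(2 × 0.09/3,782) = 0.69 points. For b = 0.5, b/SE = 0.72 and rejection is 11.2%.

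**Effect on power when drift opposes the effect.** Intervention A (20% to 17.5%): SE = √(2 × 0.1875 × 0.8125/3,782) = 0.90 points. Power without drift is Φ(2.5/0.90 - 1.96), about 80%. With an opposing 0.5 points per month it is Φ(2.0/0.90 - 1.96), about 61%.

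**Limit on persistent drift.** A fall of 1.0 point per month for 20 months would remove 20 points, the whole starting rate. A fall of 0.5 would remove 10 points, half of it.

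**Curved trends.** Centre the months at -1.5, -0.5, 0.5 and 1.5, so their squares are 2.25, 0.25, 0.25 and 2.25. Under strict alternation the mean square is 1.25 in both states, so there is no quadratic bias. Under Off-On-On-Off it is 0.25 (On) against 2.25 (Off), a difference of 2 units of curvature.

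**Cost of a time term.** Under strict alternation the squared correlation between On/Off and month is 1²/(1 × 5) = 0.20, so the variance is multiplied by 1/(1 - 0.20) = 1.25. Under the balanced orders the correlation is 0 and the factor is 1.

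**The case against.** The design is a reasoned choice. For a single facility, alternation is better than a simple before/after comparison: two Off months followed by two On months would have a two-month offset, so alternation halves it. That stands. The offset is reduced but not removed.

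The evidence for drift is indirect. Under-reporting is a level, and constant under-reporting produces no trend. The article links it in particular to reports sent to hospital administration, whereas here events go into the medical record, after vignette training and a preparation period of about six months. These safeguards should help completeness and consistency. They do not take a trend out of the On-Off contrast, but they are reasons not to assume a large one.

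A reader might infer that drift biases all five interventions in the same direction, and in their favour. The text does not support this: the starting state is shown only in Figure 1, and nothing in the text says that it is the same in every block. A reader might also take 1.0 point per month (40% of the target, 19% rejection) as the typical size. Such a fall could act only for a short time.

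Nor is a balanced order better against every trend. It removes linear drift but is exposed to curved trends within a block, such as fatigue that levels off or a seasonal peak, whereas strict alternation has no quadratic bias.

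The article mentions selecting confounders for multivariate modelling, which might be read as covering time. The models it then names are for phase 0 against phase 2, and the phase 1 test is stated as a Khi-2.

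**Conclusion.** The point holds at a moderate size. Every block carries a one-month offset whose sign is not known from the text and may differ between blocks, and the stated primary phase 1 test does not adjust for it. Under assumed linear drifts of 0.3 and 0.5 points per month, the bias is 12% and 20% of the 2.5-point target, with false rejection of about 6% and 8% at a 20% rate, and about 11% for a drift of 0.5 at a 10% rate. Slower drift does little harm: 0.25 points per month gives 5.8% at a 20% rate. The slopes are assumptions, and the documents do not show that reporting declines.

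The label conflict does not depend on any of these figures. The Abstract's cRCT and the Methods' quasi-experimental design must be reconciled. It would go too far to conclude that the registration describes a randomisation that never took place, because the registry record was not available and only the Abstract's sentence can be judged.

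**What to change.** 1. **Label.** Reconcile the Abstract's sentence and the registration with Study design by removing cRCT, unless the order of periods is actually randomised. This costs a text correction and a registry edit.

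2. **Order or analysis, settled before phase 1** (Trial status reports phase 0 still under way). Choose one:
   - **Balanced order.** For each of A to E, draw at random Off-On-On-Off or On-Off-Off-On, and add a linear calendar-time term to the per-block analysis. Duration and sample size do not change, and the time term costs essentially no precision. The downsides are exposure to curved trends within a block and two consecutive months in the same state. For an Off-first block it saves no changeovers: counting the later permanent use, Off-On-Off-On and Off-On-On-Off both need three.
   - **Keep the alternation.** Replace the plain Khi-2 with a per-block logistic model containing On/Off and linear calendar time. The variance of the On-Off effect rises by about 25%. Using power = Φ(z/√1.25 - 1.96), with z the target divided by its unadjusted SE, power for A falls from about 80% (z = 2.79) to about 70%, and for B from about 84% (z = 2.95) to about 75%. C (z = 3.16), D (z = 3.44) and E (z = 3.85) stay above 80%.

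Neither option cures random month-to-month variation. With two months per state, an assumed between-month SD of 1 point at a 20% rate would by itself raise the false rejection rate of the patient-level test to about 18%.

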**Figure 1 F1:**
[figure not shown]
**The multifaceted intervention.** This figure presents the different components of the multifaceted intervention, as well as the alternate-month design.

There are two 2-month observational phases: a “pre-intervention” phase (phase 0) and a “simultaneous interventions A to E” phase (phase 2) see Figure 1.

### Setting

This study takes place at an adult OED, at a university teaching hospital over a 24-month period. It is open 24 hours a day, 7 days a week and handles all types of medical and surgical ophthalmological emergencies. The unit treats approximately 22,600 patients per year, i.e. an average of 62 patients a day.

### Participants

#### Patients and those accompanying them

All patients registering at the OED are included in the study. Those accompanying the patient (family, friends, etc.) are also enrolled.

#### Health care professionals and administrative staff

The OED team (7 nurses, 6 ward aides, 2 orthoptics students, 7 residents in ophthalmology and 4 senior ophthalmologists) operating on a rotating schedule to provide care 24/7 are enrolled in the study. The OED team present during a week day is composed of 4 nurses, 4 ward aides, 2 orthoptics students, 1 or 2 residents in ophthalmology, and 1 on-call senior ophthalmologist. Four admitting clerks are also enrolled.

### Intervention

This program is based on the successive implementation of five complementary interventions (Interventions A to E).

#### Intervention A (organizational approach): standardized triage algorithm and patient waiting number screen

The first intervention will be based on the implementation of a standardized computer algorithm for patient triage as soon as they arrive in the unit. This enables the degree of urgency of care to be calculated, the order in which the patient is to be seen by a medical doctor to be specified and related medical procedures to be started. The unit has developed its own algorithm specifying 6 levels of severity from lowest to highest. The first level indicates a non-emergency situation whereas level 6 designates the need for immediate care. Triage is performed at reception by a nurse trained on the algorithm, which will enable unit staff to know how many patients are waiting for care, the level of severity for each patient, and length of time each has been waiting.

A patient waiting number will be based on the triage algorithm. This number and the consultation room will be displayed on a video screen in the waiting room when the patient is called. Nursing staff will come to the waiting room to get patients who cannot read the screen (as they used to do before implementation of the algorithm and patient waiting number screen).

This algorithm will involve both informatics technology (IT) revisions and staff process/culture changes to address the admission process. IT revisions will include integrated interfaces between the OED computer system (admission, triage, OED record) with the hospital computer system [22].

#### Intervention B (environmental approach): clear signage of the premises

Appropriate signage may be a factor for the prevention of aggressive behavior and insistent questions. We will create new signage to help patients to understand where to go between the hospital admission desk, the waiting rooms, the nurse office and the consultation rooms. The sequence varies depending on the day of the week (week or weekend) and the time of day (daytime or night time).

#### Intervention C (educational approach): informational videos for patients and accompanying persons in waiting rooms

There will be video screens in each waiting room displaying information for patients and accompanying persons, i.e. profile of medical staff, average number of consultation per day, rules for provision of care and the average patient waiting time, as well as general-interest educational information on eye diseases. This enables patients to understand the reason for their wait and makes the wait more bearable.

#### Intervention D (human approach): mediator in waiting rooms

There will be a mediator in the waiting rooms in order to liaise between the patients and those accompanying them and the medical staff in the event of a problem. This mediator will intervene in order to deal with any uncivil or aggressive behavior, and to prevent an escalation to violence as well as to reduce tension in the unit. Their role will also involve identifying individuals presenting a risk in order to quickly intervene in the event of a minor incident so as to prevent the situation from deteriorating.

#### Intervention E (security approach): surveillance camera linked to hospital security

The final intervention will involve installing surveillance cameras throughout the unit (admissions desk, waiting rooms, corridors, and consultation rooms) linked to the hospital security post. These cameras will be signposted. The fact that these cameras are signposted enables a dissuasive approach to the prevention of uncivil or violent behavior.

